### Randomization

Participants will be randomly assigned in a 1:1 ratio to either the intervention or control group using the TextIt platform’s “split randomly” function. This function distributes contacts equally across pathways, ensuring allocation to either the intervention or control condition. Randomization will occur only after a participant has given birth.

### Follow-Up Assessments

All participants will be asked to complete follow-up surveys at 6 weeks post partum and 6 months post partum. To encourage completion, reminder SMS text messages will be sent every other day for up to 2 weeks (a maximum of 6 reminders) or until the survey is submitted. After day 14, an email will be sent to participants who have not yet completed the survey as a final reminder. If no email address was provided, an extended SMS text message will be sent instead. Participants may also be contacted by phone to encourage survey completion within this 2-week window.

### Blinding

Due to the complex nature of Essential Coaching Postpartum, participants cannot be blinded and will be informed of their group allocation. To minimize blinding of personnel in relation to data collection, no hospital staff (eg, nurse midwives, physicians, and other health care providers) will be aware of participant involvement in the study. This is feasible because Essential Coaching Postpartum is delivered directly to participants’ personal mobile phones, with no in-person intervention. The research team will be aware of participant allocation and will track data collection but will not be involved in the randomization process, which occurs automatically through the TextIt platform. As all study procedures are conducted remotely through a preconfigured system, the research team has no direct interaction with participants, thereby reducing any risk of influencing participant responses.

### Sample Size

Sample size calculations were conducted with the assistance of a statistician for both birthing and nonbirthing parents to ensure adequate numbers for each group. As the parent dyad objective is exploratory, no formal calculation was performed for dyads. In the original RCT [25], the baseline parenting self-efficacy score for birthing parents was 35, which is considered clinically low. This value was used for this analysis. On the basis of the SD from the original RCT [25], an improvement of 4 points in the intervention group at 6 weeks is anticipated, which would no longer be classified as clinically low. A total sample size of 141 parents is therefore required, assuming 80% power and a 2-tailed α of .05. As no comparable evidence is available for nonbirthing parents, we will apply the same sample size estimation (n=141) for nonbirthing parents. Allowing for 15% attrition, we plan to recruit a minimum of 166 birthing parents and 166 nonbirthing parents.

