### Primary Outcomes

Parenting self-efficacy will be measured using the Karitane Parenting Confidence Scale [40]. This 15-item tool assesses perceived self-efficacy among parents of infants aged birth to 12 months of age and has acceptable internal consistency (Cronbach α=0.81) and test-retest reliability (*r*=0.88) [40]. A cutoff score of 39 or less (out of 45) indicates clinically low perceived parenting self-efficacy [40].

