### Data Analysis

Data will be analyzed on an intention-to-treat basis. Demographic characteristics, including parental age, marital status, educational level, and delivery method (eg, vaginal or cesarean), will be summarized using means and SDs or percentages, as applicable. Postnatal health care contacts for the parent and infant, health concerns, and feeding behavior will also be reported using means and SDs or percentages, as applicable. Any significant differences in baseline characteristics, assessed using chi-square tests or Mann-Whitney *U* tests, will be adjusted for in subsequent analyses. A *P* value of <.05 will be considered statistically significant for all outcomes.

For the primary and secondary outcomes, analysis of covariance will be used to determine whether scores differ between the 2 groups, with adjustments for pretest scores and any significant baseline characteristics. For the exploratory analysis, dyadic actor-partner interdependence multivariate multilevel modeling will be used to examine each dyad member’s relationship to primary and secondary outcomes after accounting for other explanatory variables. For implementation data, quantitative responses will be reported, and thematic analysis [48] will be conducted to describe participants’ experiences with Essential Coaching Postpartum.

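### The sample-size rationale is false on the plan's own cut-off (35 + 4 = 39 is still clinically low), and it words the 4 points as a gain within the intervention arm although the trial tests a between-group difference

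*Protocol article*

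**What the plan says.** All of the following is in the protocol article.

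- **Starting value (Sample Size).** In the earlier trial, "the baseline parenting self-efficacy score for birthing parents was 35, which is considered clinically low". The section adds that this value was used for the present calculation.
- **Effect (Sample Size).** The sentence opens "On the basis of the SD from the original RCT" and continues that "an improvement of 4 points in the intervention group at 6 weeks is anticipated, which would no longer be classified as clinically low". No numeric SD, control-arm score, control-arm change or between-group difference is printed.
- **Size (Sample Size).** "A total sample size of 141 parents is therefore required, assuming 80% power and a 2-tailed α of .05". For the primary population: "As no comparable evidence is available for nonbirthing parents, we will apply the same sample size estimation (n=141) for nonbirthing parents". Then: "Allowing for 15% attrition, we plan to recruit a minimum of 166 birthing parents and 166 nonbirthing parents".
- **Cut-off (Primary Outcomes).** "A cutoff score of 39 or less (out of 45) indicates clinically low perceived parenting self-efficacy".
- **Test (Data Analysis).** "analysis of covariance will be used to determine whether scores differ between the 2 groups", adjusting for the pretest score and for baseline characteristics that differ significantly. The Primary Hypothesis likewise compares the programme with standard care at 6 weeks.

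**The concern.** There are two faults in one sentence.

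First, the clinical meaning offered for 4 points is that it takes parents out of the clinically low range. On the printed figures it takes them to the top of that range, not out of it. Left as it is, a 4-point result could be reported as having crossed a threshold that it has not crossed.

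Second, the 4 points is worded as a gain in the intervention arm, anchored to the baseline of 35. The test is of intervention against control. A within-arm gain equals the between-arm difference only when the control arm's change is zero, and the plan does not say that it expects this. Baseline falls within about a week of a first birth, and controls keep standard education and care and may seek other support, so some change in that arm is plausible. If 4 points really was a within-arm gain, the stated 80% power does not describe the planned comparison. The same 141 carries over to nonbirthing parents, so the primary test is affected too.

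**Working it through.** **1. Cut-off.** Inputs: baseline 35, improvement 4 (Sample Size); clinically low is 39 or less (Primary Outcomes).

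35 + 4 = 39, and 39 ≤ 39, so the result is still clinically low. This step needs no SD and no outside figure.

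**2. The plan's own sample size.** Inputs: total 141, 1:1 allocation, two-sided α 0.05, power 80%, 4 points. The SD is not printed, so 141 cannot be reproduced forwards. It can only be solved backwards, on the assumption that 4 points was entered as a between-group difference in a two-sample comparison.

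- Normal approximation: d = 2 × (1.960 + 0.842) / √141 = 0.472, so SD = 4 / 0.472 = 8.48.
- t-based: d = 0.475, so SD = 4 / 0.475 = 8.42.
- Forward check (normal approximation): SD 8.4 gives a total of 140 and SD 8.5 gives 142, so 141 is consistent with this reading.
- Attrition: 141 / 0.85 = 165.9, so 166 reproduces.

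**3. The back-solved SD is not unique.** If the between-group input had been 3 points, 141 at 80% power would imply SD = 3 / 0.475 = 6.31. The documents cannot tell these two readings apart.

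**4. Illustration of a control-arm gain.** Assumptions: SD 8.42 as in step 2; the intervention arm gains 4 points; controls gain 1 or 2 (assumed values). The between-group difference is then 4 − 1 = 3 or 4 − 2 = 2. For the ANCOVA, the residual SD is 8.42 × √(1 − r²), where r is the correlation between baseline and 6-week scores. The documents do not give r, so I show 0.5 to 0.7: residual SD 7.29 at r = 0.5, 6.73 at 0.6 and 6.01 at 0.7. This takes 8.42 to be a raw SD.

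| Control gain | Between-group difference | Power at 141, unadjusted | r = 0.5 | r = 0.6 | r = 0.7 |
|---|---|---|---|---|---|
| 0 | 4 | 80% | 90% | 94% | 98% |
| 1 | 3 | 56% | 68% | 75% | 84% |
| 2 | 2 | 29% | 37% | 42% | 50% |

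**The case against.** The cut-off error has no real defence. An unrounded baseline slightly above 35 would escape it, but the article prints 35 and says that this value was used.

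On the rest, the case against has force, and most of it stands.

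- **141 may be right.** A reader might infer that the trial is underpowered. The documents do not support that. The statistician may well have entered 4 points as the between-group difference, in which case the second fault is only one of wording. The lower powers rest on an SD that was itself obtained by assuming a 4-point between-group input. With 3 points and an SD of 6.31, power at 141 is 80%, not 56%.
- **The planned test adjusts for baseline.** Unadjusted figures understate power if the SD used was a raw SD. At r = 0.7 a 3-point difference would still have more than 80% power. It is therefore not established that 80% power requires a full 4 points.
- **The cut-off is not the only basis for the effect.** The sentence also appeals to the earlier trial's SD. Nor does any planned test or success criterion use the cut-off: success is judged on scores at P<.05. The error lies in the rationale, not in an endpoint.
- **Missing figures are not the fault.** The SD and control-arm values may sit in the full protocol. The criticism is of what the article states, not of what it leaves out.

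A reader might also infer that the target should rise to 5 points (40 against 35) so that the claim becomes true. It should not. That would again assume no change in controls, would fit the effect to a threshold without evidence for it, and is an arbitrary step, since a group mean need not be a whole number to exceed 39.

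**Conclusion.** The point holds in two parts and should be fixed. The statement that a 4-point improvement from 35 leaves the clinically low range is false on the plan's own cut-off; this is exact and rests on no assumption. The 4 points is also described as a gain within the intervention arm, although the tested quantity is a between-group difference at 6 weeks. That is wrong as written, but whether it affects the calculation or only its wording cannot be settled from the article.

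The possible loss of power is conditional. It needs three things to be true together: 4 points was the expected within-arm gain, controls also improve, and the SD is about 8.4. The powers in the table for a control gain of 1 or 2 points are therefore illustrations, not estimates for this trial. The total of 141 and the recruitment target of 166 per parent type are not shown to be wrong.

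**What to change.** Revise the effect sentence in Sample Size and leave recruitment as it is.

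1. Delete or correct the claim about no longer being clinically low, so that a 4-point gain from 35 is not presented as leaving that range. Do not raise the target to make the claim true.
2. State the powered quantity as the between-group difference in self-efficacy score at 6 weeks. If 4 points was entered as that difference, saying so is enough.
3. If 4 points was the expected gain within the intervention arm, subtract the expected control-arm change and restate the power at 141 for the resulting difference, using the SD actually used in the calculation and saying whether that SD already allows for baseline adjustment.

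The cost is one sentence of wording and, in the third case, one recalculation. No extra participants are needed, although the stated power may become less favourable. The article reports 11 birthing and 5 nonbirthing parents enrolled by September 15, 2025, so the correction can be made well before outcomes are analysed.

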### Program Content and Design

Essential Coaching Postpartum consists of 2 separate but related evidence-based programs: Essential Coaching for Every Mother, which provides SMS text messages for the birthing person, and Essential Coaching for Every Partner, which provides SMS text messages for the nonbirthing parent. Both were co-designed with parents and postpartum health care providers [24,27] and are aligned with the *Loving Care* book series [28-31]. Essential Coaching Postpartum includes 59 SMS text messages: 2 messages per day in the first 3 weeks and daily messages in the next 3 weeks. Topics include postpartum mental health, self-care, postnatal follow-up, feeding, infant concerns, cord care, well-baby care, normal development, crying, and safe sleep. Parents can choose to receive messages related to breast or chest feeding, formula feeding, or combination feeding and can change their preference at any time. Messages are timed according to the infant’s date of birth and personalized with the infant’s name. All messages are free to receive; however, optional embedded links may generate data charges if accessed.

All participants, regardless of group allocation, will receive a welcome message from Essential Coaching Postpartum as well as reminders to complete the surveys. Participants may withdraw from the study at any time by texting “stop” to the study mobile phone number, after which they will no longer receive messages or be asked to complete additional surveys.

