### Eligibility Criteria

Participants will be recruited prenatally and postnatally. To pre-enroll prenatally, eligible birthing parents will (1) be pregnant (>28 wk) with their first child, (2) understand English, (3) have a mobile phone with SMS text messaging functionality and a data plan, and (4) live in Nova Scotia. Eligible nonbirthing parents will (1) have a pregnant (>28 wk) partner (ie, the birthing parent) expecting their first child or will be expecting their first child via an alternative method (eg, adoption or surrogacy), (2) understand English, (3) have a mobile phone with SMS text messaging functionality and a data plan, and (4) live in Nova Scotia. Participants who pre-enroll prenatally will only be considered enrolled and assigned a study number once they text “birth” to the study mobile phone number and are randomly assigned.

To enroll postnatally, eligible birthing parents will (1) be early postpartum (<7 d) with their first child, (2) understand English, (3) have a mobile phone with SMS text messaging functionality and a data plan, and (4) live in Nova Scotia. Eligible nonbirthing parents will (1) be early postpartum (<7 d) with their first child, (2) understand English, (3) have a mobile phone with SMS text messaging functionality and a data plan, and (4) live in Nova Scotia.

Participants (both birthing and nonbirthing parents) will be excluded if they (1) have a newborn who dies or is expected to die before leaving the hospital; (2) have no access to a mobile phone, either personal or shared; (3) are unwilling to receive SMS text messages; (4) decline participation or withdraw; or (5) participated in a previous iteration of this project (eg, development or evaluation). Parents are not required to participate as dyads to be inclusive of all family compositions; however, involvement of the other parent, if applicable, will be encouraged. Participants who do not fully complete the baseline survey will be considered withdrawn from the study. If the participant was randomly assigned to the intervention, they will continue to receive the messages, but no further data will be collected from them.

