### Control Group

Participants will receive the standard education provided at the hospital in which they give birth. After enrollment, participants in the control group will not receive any Essential Coaching Postpartum SMS text messages. They are not restricted from seeking additional postpartum support outside of the study. They will continue to have access to standard perinatal care, including mental health services available through primary care providers and community resources. At enrollment, 6 weeks post partum, and 6 months post partum, participants will be sent an SMS text message with a link to complete the follow-up survey.

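### The only opt-out described ends the surveys as well as the messages, which creates an avoidable risk of arm-related missing outcomes

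*Protocol article*

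**What the plan says.** Under Program Content and Design, the article makes a text of *stop* the way to withdraw from the trial, at any time and for either arm. It then gives the consequence: "after which they will no longer receive messages or be asked to complete additional surveys". No other opt-out is described.

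The same section gives the message load: "Essential Coaching Postpartum includes 59 SMS text messages: 2 messages per day in the first 3 weeks and daily messages in the next 3 weeks". Intervention Group says that these messages continue until 6 weeks post partum. Control Group says that "participants in the control group will not receive any Essential Coaching Postpartum SMS text messages". Participants in both arms "will receive a welcome message from Essential Coaching Postpartum as well as reminders to complete the surveys".

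On analysis, Data Analysis says: "Data will be analyzed on an intention-to-treat basis". The method is analysis of covariance, adjusted for pretest scores and for baseline characteristics that differ significantly. Primary Hypothesis places the main comparison at 6 weeks. Secondary Outcomes lists unsubscription rates among the implementation measures.

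On contact routes, Follow-Up Assessments says: "After day 14, an email will be sent to participants who have not yet completed the survey as a final reminder". It adds that an extended text replaces the email where no address was given, and that phone contact may also be used.

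**The concern.** Ending an intervention and leaving a study are different decisions. An intention-to-treat comparison needs outcomes from people who make only the first. Here one keyword carries both meanings. A parent who finds two texts a day too many, or who no longer needs them, has no described way to say so and still be sent the surveys.

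Both arms can use the keyword, but a wish to end the coaching messages can arise in only one. If some intervention parents use it for that purpose, their outcomes are missing because of the treatment they were assigned. Adjustment for baseline scores helps only as far as baseline predicts who stops and how they fare. It cannot capture a reaction to the messages that develops after baseline. An analysis plan may set out how missing values are handled, but no analysis can recover a survey that was never sent.

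**Working it through.** **1. The plan's own figures.** Sample Size asks for 141 analysable parents of each type and allows 15% attrition: 141 / (1 − 0.15) = 165.9, rounded up to 166. This agrees with the article. The 15% is an overall figure and is not split by arm.

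**2. What each arm receives, and what *stop* ends.**

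| | Intervention | Control |
|---|---|---|
| Programme messages | 59 in the full programme, until 6 weeks | none |
| Welcome message, survey links, reminders | yes | yes |
| Ended by *stop* | messages and all later surveys | all later surveys and reminders |
| Way to end messages only | none described | no programme messages to end |

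**3. Timing.** Programme messages run up to the 6-week point. A parent who stops in order to end them therefore does so before the 6-week survey. Both remaining assessments, at 6 weeks and 6 months, are lost.

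**4. Effect on the estimate (illustration; all rates and gaps are assumed).** Let p be the proportion in an arm who stop, and g the completer mean minus the stopper mean. The arm mean is (1 − p) × completer mean + p × stopper mean, so the completer mean exceeds the arm mean by p × g. If g is the same in both arms:

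shift in the between-arm difference = (p intervention − p control) × g

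- 10% v 2%, g = 4: 0.08 × 4 = 0.32 points, which is 8% of the planned 4-point effect.
- Rate difference of 4 percentage points, g = 4: 0.04 × 4 = 0.16 points (4%).
- Rate difference of 15 percentage points, g = 4: 0.15 × 4 = 0.60 points (15%).
- With g = −4 (stoppers do better), the same sizes appear with the opposite sign.

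Because the model adjusts for pretest score, g should be read as the gap left after that adjustment.

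A wider check varied total loss by arm while holding the average at 15%. With the same gap in both arms, the shift is (0.20 − 0.10) × g at 10% control and 20% intervention loss, and (0.25 − 0.05) × g at 5% and 25%. For g from 2 to 8 this gives 0.2 to 0.8 and 0.4 to 1.6 points. If only intervention-arm loss is informative, the shift is p intervention × g. Its extreme is 0.25 × 8 = 2.0 points, which needs the most unequal loss, the largest gap and one-sided informativeness together.

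**5. Effect on power.** The article does not print the SD. Solving back from 141 gives SD = 4 × √(70.5 / 2) / (1.960 + 0.842) = 8.48. With 83 randomised per arm (166 / 2) and power = Φ(4 / (8.48 × √(1/n₁ + 1/n₂)) − 1.96):

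| Loss, control / intervention | n₁ / n₂ | Power |
|---|---|---|
| 15% / 15% | 70.55 / 70.55 | 80.0% |
| 10% / 20% | 74.7 / 66.4 | 79.9% |
| 5% / 25% | 78.85 / 62.25 | 79.5% |

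At the same overall attrition, uneven loss costs about half a percentage point of power. What is at risk is bias, not precision.

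**The case against.** The strongest reply is that the article defines *stop* as study withdrawal, for both arms, and that ending surveys for someone who withdraws is correct. How parents would use the keyword is inference. The welcome text, consent wording and message scripts are not shown. Controls know their allocation and can receive up to 6 text reminders per follow-up survey, so they too may quit. All of this stands. It means that the imbalance is a risk of unknown size, not a demonstrated fact. It does not answer the point that the article fixes one opt-out with two consequences and describes no lesser one.

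Several stronger readings are tempting, but the documents do not support them:

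- *The rule contradicts intention-to-treat.* It does not. Missing outcomes weaken a comparison by allocation, but parents can still be analysed as randomised. The article does not commit to complete cases only, and missing-data handling may properly be in an analysis plan not shown.
- *The bias flatters the programme.* That requires stoppers to fare worse. Confident parents who feel no need of the messages may stop too, which reverses the sign. The article has no data on either.
- *Withdrawn parents' earlier outcomes are discarded.* Eligibility Criteria lists those who "decline participation or withdraw" among the exclusions, but nothing there says that data already collected are removed.
- *Stops use up the attrition allowance in one arm.* The allowance is overall. Rates of 10% and 2% average 6%, well inside 15%, and step 5 shows that imbalance hardly affects power.

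**Conclusion.** The point holds as a design weakness that is cheap to remove. The only opt-out described joins ending the messages to ending follow-up. The programme messages exist in one arm only and finish at the primary time point. Intervention parents who want only the messages to end would therefore be missing at both 6 weeks and 6 months.

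The size and direction of any bias cannot be known from the article. With assumed rate differences of 4 to 15 percentage points and an assumed 4-point gap common to both arms, the shift is 0.16 to 0.60 Karitane points either way. That is modest beside the planned 4 points, and baseline adjustment would remove any part that pretest scores predict. Larger values need more extreme assumptions. The case for acting rests on how easily the loss can be prevented, not on a large expected bias.

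**What to change.** Offer two distinct actions: ending the programme messages, and leaving the study.

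- Explain both in the welcome message and in the automatic reply to *stop*.
- For parents who end only the messages, keep sending the 6-week and 6-month surveys. Use email where an address is held, and phone or another agreed route where it is not. The present fallback for a missing address is another text, so the route should be agreed with the parent.
- End surveys only for those who choose to leave the study.
- Report both actions by arm, next to the unsubscription rates already planned.

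This looks feasible with what is in place. Surveys run in REDCap, apart from the messaging platform, and email and phone contact are already used. Eligibility Criteria already separates the two in the other direction: intervention parents with an incomplete baseline keep the messages but give no further data.

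The cost is a small ethics and consent amendment in a trial already recruiting, one extra TextIt branch, and one extra contact for a few parents. By September 15, 2025, 11 + 5 = 16 parents were enrolled of a planned 166 + 166 = 332 (about 5%), so an amendment made near that date would cover nearly all of the trial.
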